## Statistical analysis

4

### Statistical analysis and development of the score

4.1

All statistical analyses will be conducted using R packages. Initially, a univariate analysis will be performed to examine the relationship between each pre- and intraoperative variable in the database and the primary outcomes. Variables with *p* ≤ 0.20 and ≤10% missing data will be considered for inclusion in a multivariable model, to ensure sensitivity and prevent the exclusion of potentially relevant factors. Among collinear variables, selection will be based on *p* values and their potential use in constructing an outcome score.

In the multivariable analysis, intraoperative variables will be entered independently and in combination with preoperative variables into a logistic regression model. Both forward and backward stepwise selection procedures will be employed (with entry criteria *p* ≤ 0.10 and inclusion criteria *p* ≤ 0.05) for outcomes of interest. The final model will be selected based on the Akaike Information Criterion (AIC). Variables that independently predict major complications or death will be considered as candidates for the risk index score. Alternative combinations of variables for the risk index score will be compared, emphasising simplicity, clinical safety, and predictive power.

After determining the final variables for inclusion, the magnitude of the β coefficients from the regression equation will be used to assign weights to each variable. Depending on the number of variables included, the score will be represented as either a 10-point or a 20-point scale. The intervals and cut-offs for each point level will be designed to ensure that a 1-point increase in the score corresponds to a proportional increase in the odds of a complication. The values for each cut-off will then be rounded to clinically relevant figures that can be recalled easily by surgeons. For instance, operation duration will be valued as follows: 0 points for ≤120 min, 1 point for 120–180 min, etc.

Logistic regression will be used to examine the relationship between major complications/death, and the risk index score (treated as an ordered categorical variable based on predefined categories) and its components across the three patient cohorts. Model discrimination will be assessed by calculating c-statistics (area under the receiver operating characteristic curve). For model calibration, the Hosmer-Lemeshow (HL) goodness-of-fit test will be used to compare predicted versus observed outcomes between the two cystectomy cohorts. In the final cohort, differences in complication rates across individual scores will be compared using chi-square tests. Additionally, using morbidity (complicated/uncomplicated) and mortality (dead/alive) as dichotomous dependent variables, multiple logistic regression models will be derived. Overall model significance will be assessed via the model chi-square statistic, and differences between observed and expected outcomes will be evaluated using the HL test.

To develop the surgical difficulty index, pre-, intra-, and postoperative parameters and outcome measures will be determined by experienced high-volume surgeons (≥1000 major interventions and >10 yr of surgical experience) using the Delphi method. Pre- and perioperative parameters that potentially increase operative difficulty and risk will be assessed using a 5-point scale, as shown in Supplementary Tables 1–3. Primary outcome measures for surgical difficulty will include operation duration, blood loss and transfusion, use of haemostatic agents, and the surgeon’s judgement (on a scale from 0 to 100).

The performance of the universal surgical risk calculator, which includes multiple specialities and hundreds of procedures, will be compared with the performance of our risk calculators, specifically programmed for this score development. This comparison will be made for individual procedures (eg, RC and RP).

Alternatively, to create risk prediction models, random-intercept, fixed-slope hierarchical models (using SAS GLIMMIX) will be employed. These models account for case clustering within hospitals and impose an empirical Bayes-type shrinkage adjustment. As a result, both universal and procedure-specific surgical risk calculators will be developed. The performance of the universal versus procedure-specific models will be evaluated using three metrics: the c-statistic, the HL statistic (in a revised graphical form), and the Brier score.

Prediction models for mortality, CCI, blood loss, operating time, and other outcomes will be developed using logistic regression with stepwise selection based on the AIC. Cumulative C-indices will be recorded at each step of model development.

Given the HL test’s sensitivity to sample size, graphs will be constructed based on sequential groups with equal observed events rather than equal patient numbers (thus, low-risk groups will have more patients than high-risk groups).

For evaluating risk prediction accuracy and comparing the universal and procedure-specific surgical risk calculators, the Brier score will be considered the most appropriate measure of model performance. Results from 2 yr of data used for model development will be compared with those from the 3rd year of data used for validation.

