### Study aims

2.2

The final Delphi document will aim to synthesise expert consensus and provide guidance in areas of on-going debate within the field of urological surgery. Its findings will be of significant relevance and potential applicability to other surgical disciplines, ensuring the dissemination of optimised guidance to clinicians and patients alike. Ultimately, these position statements will be incorporated into internationally recognised guidelines issued by urological associations.

The primary objective of this study will be to develop a peri- and intraoperative risk prediction index and scoring system to estimate and quantify surgical difficulty, as well as to construct targeted, organ-specific scoring systems based on pre- and intraoperative factors. Similar to the existing renal scoring systems [8,9,11], the objective will be to establish a checklist-based framework to assist in surgical planning, case selection, and stratification of procedures based on their suitability for teaching purposes (see Fig. 1B).

The main objectives of the study will be the following (Table 4):1.To predict intraoperative (during intervention), perioperative (in-hospital period), and postoperative (within a defined period after intervention) outcomes by considering both pre- and intraoperative factors2.To predict intra-, peri-, and postoperative outcomes based solely on preoperative factors, thereby optimising resource allocation and enabling the identification of appropriate teaching cases prior to surgery3.To define surgical difficulty as an independent metric for the comparative analysis of intra-, peri-, and postoperative outcomes across surgeons and procedures. This will necessitate the delineation of parameters contributing to surgical complexity from both an anaesthetic and a surgical perspective. Consideration will be given to anaesthetic and surgical case volume, frequency of procedures over a given timeframe, and individual learning curves, as these factors will influence both case complexity and the risk of complications4.To develop multiple indices for surgical risk and difficulty estimation, which will be calculated both preoperatively and immediately postoperatively

**Table 4 t0020:** Study aims

#	Aim
1	To predict intra-, peri-, and postoperative outcomes by considering pre- and intraoperative factors

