2	To predict intra-, peri-, and postoperative outcomes by considering preoperative factors only, to optimise the allocation of critical care resources or defining teaching-appropriate cases before surgery starts
3	To determine surgical difficulty as a separate matter to judge surgical performance by improving the comparison of intra- and postoperative outcomes between surgeons and between different interventions
4	To define parameters that make certain operations (and approaches) for anaesthetists and urologists more difficult
5	To create several indices (surgical risk and difficulty estimation) that are calculated before and immediately after surgery

The surgical difficulty and risk estimation tool will integrate five categories of patient-specific parameters (Table 2):1.Preoperative (known, expected) patient-specific characteristics and conditions (eg, body mass index [BMI], ASA score, sex, prior abdominal surgery, and comorbidities)2.Intraoperative (unknown or unexpected) body/patient-specific characteristics and conditions (eg, bleeding tendency, restricted operative space due to a narrow bony pelvis, or extensive adhesions)3.Preoperative targeted organ-specific parameters (eg, tumour size and location, organ anatomy and morphology, or a history of prior interventions on the targeted organ such as biopsies or transurethral resection of the prostate preceding prostatectomy)4.Intraoperative targeted organ-specific parameters (eg, fibrosed periprostatic tissue or tumour extension beyond the targeted organ).5.Unexpected/unknown postoperative conditions prior to discharge or within 24 h (eg, acute kidney injury, quantified by a decrease in glomerular filtration rate [ml/min])

Surgical and anaesthetic parameters will be evaluated independently to account for the influence of case volume and individual learning curves on surgical complexity and risk. The key variables will include the total case volume, frequency of procedures performed within a defined period, and complexity of prior cases. Additionally, institutional case load will be considered when estimating perioperative morbidity risk (eg, in tertiary referral centres).

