### Development of the risk and difficulty stratification index

3.6

Following the consensus phase, the next step is to develop the formula for the risk prediction index. In this phase, the weights assigned by both surgeons and anaesthetists (ie, the median reference value) will be incorporated into a formula, which will then be normalised to a value ranging from 0 to 100. Similar to the Comprehensive Complication Index (CCI) formula [23,24], variables may be included to ensure that the model assigns higher values for multiple and severe complications while yielding lower values for single and minor peri- and postoperative complications. This approach will enhance the precision of differentiating between the severity and impact of pre- and postoperative risk factors. Organ-specific scoring systems will be developed following the same methodology.

Based on the outcomes of the Delphi process, we will determine whether a single formula or index is sufficient to address all three objectives outlined or whether multiple indices are required. Specifically, one index may be necessary to assess preoperative factors alone (eg, to enhance decision-making, optimise the allocation of critical care resources, or designate surgeries as teaching cases), while another index may be needed to incorporate both pre- and intraoperative factors for broader objectives. If surgical difficulty requires an independent calculation, a third distinct index may be warranted.

As highlighted previously, a surgeon’s learning curve—defined by a cumulative case volume—is a critical factor. This curve will be stratified into experience-based stages: 0–20 cases, 21–50 cases, 51–100 cases, 101–250 cases, 251–500 cases, and >500 cases. Proficiency typically plateaus after approximately 500 cases.

The assertion that surgical proficiency plateaus after around 500 cases is supported by studies analysing learning curves in complex surgical procedures. Research using a cumulative sum (CUSUM) analysis and other models has demonstrated that significant improvements in performance metrics—such as operative time, complication rates, and technical outcomes—tend to stabilise after approximately 500 cases, particularly in highly complex surgeries [25,26].

This stratification serves two purposes: (1) it allows the estimation of how increasing surgical experience reduces case difficulty and risk, and (2) it helps determine whether a procedure is suitable for a teaching setting.

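### The univariable p ≤ 0.20 screen can exclude surgeon experience or centre case load when case mix masks their effect, although the plan requires both and says the screen protects relevant factors

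*Protocol article*

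**What the plan says.** Section 4.1 begins with a univariate analysis "to examine the relationship between each pre- and intraoperative variable in the database and the primary outcomes". Variables with p ≤ 0.20 and at most 10% missing data "will be considered for inclusion in a multivariable model, to ensure sensitivity and prevent the exclusion of potentially relevant factors". Forward and backward stepwise selection follows, "with entry criteria *p* ≤ 0.10 and inclusion criteria *p* ≤ 0.05", and the final model is chosen by AIC. No variable is exempted from the screen and none is forced into the model.

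Elsewhere the article commits itself to experience and volume as predictors:
- Section 3.6 treats the surgeon's learning curve as critical. "This curve will be stratified into experience-based stages", six in all, from 0–20 cases to more than 500. One stated purpose is to estimate how growing experience lowers difficulty and risk.
- Section 2.2 says "institutional case load will be considered when estimating perioperative morbidity risk (eg, in tertiary referral centres").
- Section 5.1 says that anaesthetic and surgical case volumes and learning curves have to be part of such tools.

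**The concern.** A univariable p-value measures the crude association. Section 3.6 itself describes two forces that act in opposite directions: patient factors such as prior radiation raise risk and difficulty, and an experienced surgeon mitigates them. If experience and case difficulty are positively correlated in the data, these forces offset each other in the crude comparison. A variable that predicts well once difficulty is in the model can then look null on its own and be removed before any adjusted model is fitted. Stepwise selection and AIC work only on what passed the screen, so they cannot bring it back.

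At stake is whether the regression-based score can carry a weight for factors the plan says it needs, and whether the stated reason for the screen is true.

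**Working it through.** The plan fixes one number here, the threshold of 0.20. It gives no estimate of how often a relevant factor would be lost, so there is no figure of its own to reproduce.

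**Inputs from the article.** Threshold 0.20 (section 4.1). Odds ratios of 1.2, 1.5 and 2.0 as weak, moderate and strong effects (section 3.7). Sample sizes 1180 (the stated requirement) and 1550 (the Bern database), both from section 3.7.

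**Assumed inputs.** Event rate 20%. n = 5000 as a larger dataset. Experience protective, OR 1/1.2 or 1/1.5 per SD. Case difficulty harmful, OR 1.5 or 2.0 per SD. Correlation ρ between experience and difficulty from 0 to 0.6. Difficulty is measured and included in the adjusted model.

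**Step 1: where the effects cancel.** Crude log OR ≈ ln(OR experience) + ρ × ln(OR difficulty). It is zero at ρ = |ln OR experience| / ln OR difficulty:
- 1/1.2 against 2.0: 0.182/0.693 = 0.26
- 1/1.2 against 1.5: 0.182/0.405 = 0.45
- 1/1.5 against 2.0: 0.405/0.693 = 0.58
- 1/1.5 against 1.5: 0.405/0.405 = 1, so no cancellation short of perfect correlation

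**Step 2: chance of failing the screen.** With m = |ln(crude OR)| × √(n p(1−p)), P(p-value > 0.20) = Φ(1.28 − m) − Φ(−1.28 − m).
- Exact cancellation: m = 0, so the probability is 0.80 at any n.
- No masking, OR 1.2, n = 1180: m = 0.182 × √(1180 × 0.16) = 2.50, probability 0.11.
- n = 5000, crude OR 1.028 (the simulated value for 1/1.2 against 2.0 at ρ = 0.3): m = 0.0276 × √(5000 × 0.16) = 0.78, probability 0.69 − 0.02 = 0.67.

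**Step 3: simulated drop rates** (300 logistic datasets per setting, standard error up to about 3 points; a dash means not reported):

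| n | OR experience | OR difficulty | ρ=0 | 0.1 | 0.2 | 0.3 | 0.4 | 0.5 | 0.6 |
|---|---|---|---|---|---|---|---|---|---|
| 1180 | 1/1.2 | 2.0 | 11% | 41% | 71% | 76% | 50% | 19% | – |
| 1180 | 1/1.5 | 2.0 | 0% | – | 1% | 8% | 35% | 72% | 82% |
| 5000 | 1/1.2 | 2.0 | 0% | 4% | 54% | 67% | 9% | 0% | 0% |
| 5000 | 1/1.2 | 1.5 | – | – | 8% | 33% | 76% | 75% | 35% |
| 5000 | 1/1.5 | 2.0 | 0% | 0% | 0% | 0% | 1% | 36% | 75% |
| 5000 | 1/1.5 | 1.5 | 0% | 0% | 0% | 0% | 0% | 0% | 0% |

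The 82% lies above the theoretical ceiling of 80% through simulation error. Beyond the cancellation point the variable passes the screen with a reversed crude OR (1.17 in row 3 at ρ = 0.5).

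**Step 4: does the dropped variable predict after adjustment?** In row 3 at ρ = 0.3, experience was dropped in 67% of datasets, and the adjusted test at 5% was significant in over 99%. At n = 1550 with the same odds ratios and ρ, it was dropped in 77% and significant after adjustment in about 80%.

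**Step 5: other settings.** With baseline risk 30%, experience OR 0.8 and difficulty OR 2.0, ρ = 0.3 gave drop rates of 75% to 84% in repeated runs at n = 1033 (two-thirds of 1550) and 76% at n = 5000. Moving ρ to 0.2 at n = 5000 brought the rate down to 7% to 12%.

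**The case against.** **The referral pattern is assumed.** Nothing in the article says that hard cases went to experienced surgeons in these databases. The aim of "enabling the identification of appropriate teaching cases prior to surgery" describes a future use of the tool. It does not show how past cases were allocated. This stands, and it is why the point is about what the screen can do.

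**Experience and case load may never meet the screen.** Table 2 lists neither. Section 3.6 gives experience its own route, a possible downward adjustment of the calculated index, and section 4.1 offers random-intercept models as an alternative. Section 3.7 says all CAMUS database variables were included but does not say whether experience is one of them. The uncertainty stands, but it does not remove the need. The adjustment is optional and has no stated coefficient, and no separate predictor selection is given for the hierarchical model. If the two factors bypass the screen, section 4.1 gives them no regression weight at all.

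**High drop rates come from settings near cancellation.** This is correct, and it limits the size of the point.

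**Centre case load was not simulated.** The Bern data are single-centre and cannot test it. In multicentre data, a test that ignores clustering tends to give p-values that are too small, which works against a drop. For case load the argument is one of principle only.

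**The sample is large.** Section 4.3 says that criticisms of stepwise selection matter less at this size. A larger sample narrows the range of correlations at risk but does not help near cancellation.

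A reader might infer three stronger things. One is that the screen would often drop experience; the 0% to 80% range does not show that. Another is that it deletes Delphi-consensus parameters; sections 3.3, 3.5 and 3.6 bring those into the indices through expert weights, a different track. The third is that the remaining weights would be confounded by who operated; the stated aims are mainly predictive, and no loss of discrimination or calibration was computed.

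**Conclusion.** The point holds in a limited form. A crude p ≤ 0.20 gate with no exemptions cannot do what section 4.1 says it does, and it sits badly with the commitments to experience and case volume in sections 2.2, 3.6 and 5.1. The chance of losing experience runs from about 0% to about 80% across plausible settings. It is high only where case mix nearly cancels the effect, and there sample size is no remedy. These figures rest on an assumed event rate, difficulty effect and correlation, and on difficulty being measured well enough to adjust for. The article does not show that cancellation occurs in these data, or that experience and case load are among the screened variables.

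**What to change.** In section 4.1:
1. State that the univariable p-value is not a gate for factors the plan already requires.
2. Pre-specify surgeon experience, in the section 3.6 strata, and centre case load, where the data are multicentre, as forced-in terms whatever their univariable p-value.
3. Shorten the remaining candidates by missingness, collinearity and clinical grounds without reference to the outcome. This includes the choice among collinear variables, which now uses p-values.
4. Keep the list within the 10 to 30 predictors assumed in section 3.7.
5. Remove the statement that the screen protects relevant factors.

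Entering every proposed parameter directly is not a workable alternative. Table 2 already has 14 + 13 + 2 + 12 + 13 = 54 entries (BMI appears twice), before any Delphi additions.

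The cost is a few degrees of freedom: five for six experience strata, and one for case load if it enters as a single linear term.

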### Internal validation

4.3

Internal validation of the prediction models will be conducted by randomly splitting the analytic dataset into two subsets: a developmental dataset (two-thirds of the total data) and a validation dataset (one-third of the total data). The C-indices, HL analyses, and Brier scores from the logistic regression analyses will be compared between the developmental model applied to the developmental dataset and the same model applied to the validation dataset.

The use of stepwise, forward-selection logistic regression has faced criticism, particularly in small samples, regarding variable selection and the accuracy of the coefficients and standard errors. However, such criticisms are less relevant when applied to the large sample sizes present in this study. To further test the robustness of the model, bootstrap resampling will be employed for the postoperative mortality model. Full-variable logistic regression models will be performed on each bootstrap sample. The variables will then be ranked by the magnitude of the Wald χ^2^ statistic, and the average rankings from the bootstrap samples will be compared with the order of entry of variables during the forward selection stepwise regression analysis. As such, all steps described above aim to minimise overfitting and improve predictive accuracy.

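### Score weights come from unshrunk β coefficients after data-driven selection and no stated step corrects them, so weights and model-based risks can be too extreme, mainly for rare outcomes and small subsets

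*Protocol article*

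**What the plan says.** Section 4.1 lays out a complete route from data to points. The screen comes first ("Variables with *p* ≤ 0.20", together with a limit on missing data). Then "Both forward and backward stepwise selection procedures will be employed", with entry at p ≤ 0.10 and retention at p ≤ 0.05, and the final model is chosen by AIC. After that, "the magnitude of the β coefficients from the regression equation will be used to assign weights to each variable". The only later operations are scaling to 10 or 20 points and rounding the cut-offs.

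As an alternative for the risk calculators, section 4.1 says that "random-intercept, fixed-slope hierarchical models (using SAS GLIMMIX) will be employed" and adds: "These models account for case clustering within hospitals and impose an empirical Bayes-type shrinkage adjustment".

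Section 4.3 describes a random two-thirds to one-third split and, for the mortality model only, a bootstrap that compares variable rankings. It argues that criticism of stepwise selection matters less in large samples, and concludes that "all steps described above aim to minimise overfitting and improve predictive accuracy".

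Sections 3.5 and 3.6 also describe weights given by surgeons and anaesthetists, so β is not the only source of weights in the article. It is the source that section 4.1 fixes for the regression-based score.

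**The concern.** A coefficient that survives a significance filter is, on average, too far from zero, because the sample in which it survived tended to overestimate it. Unless it is shrunk, a model built from such coefficients spreads predicted risks too widely: too high for high-risk patients and too low for low-risk patients. The inflation is greatest for weak predictors and rare events.

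The tool is meant for counselling, consent and comparison of surgeons and centres (section 5.1.2), so overly extreme risks would reach patients and benchmarking. A reader of section 4.3 may also think that overfitting is already dealt with.

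**Working it through.** **Does any stated step shrink the slopes?**

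- Split sample (4.3): compares C-index, Hosmer-Lemeshow and Brier results between the two parts. It measures performance and leaves β unchanged.
- Bootstrap (4.3): mortality model only. It refits full-variable models, so selection is not repeated, and it compares Wald rankings with the order of entry. It gives no optimism estimate and no correction.
- Hierarchical model (4.1): random intercept, fixed slope. The empirical Bayes shrinkage therefore acts on hospital intercepts. The fixed slopes, which would set the weights, stay unshrunk.

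So none does.

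**Inputs from section 3.7.** Up to 30 predictors; odds ratios 1.2, 1.5 and 2.0; required sample size 1180; Bern database 1550. Two-thirds for development gives 1180 × 2/3 = 787 and 1550 × 2/3 = 1033.

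The figure of 1180 serves here only as a scale, and it was not reproduced. With f² = (ln 1.2)² = 0.0332, 30 predictors, 80% power and alpha 0.05, the noncentral-F calculation gives N = 761, and 761 × 1.5 ≈ 1141, which is 3.3% lower. The plan does not state how it converts odds ratio to effect size, so this does not show 1180 to be wrong.

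**Simulation.** Assumptions that are not in the documents: 30 independent standard-normal candidates, odds ratio per SD, 10 or all 30 truly predictive at odds ratio 1.2, event rates as shown, 8 to 150 replicates per cell. Each run applied the p ≤ 0.20 screen and then backward elimination at p ≤ 0.05. The calibration slope was taken in 20,000 new patients in the main runs (1.0 means no shrinkage needed). Inflation is the mean of estimated over true β among retained true predictors. Events per candidate = n × event rate / 30.

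| Development n | Event rate | Events per candidate | Slope, OR 1.2 | Inflation, OR 1.2 | Slope, OR 1.5 |
|---|---|---|---|---|---|
| 787 | 3% | 0.8 | 0.20–0.29 | 2.9 | 0.49 |
| 787 | 20% | 5.2 | 0.57–0.59 | 1.45–1.50 | 0.87 |
| 787 | 25% | 6.6 | 0.61–0.62 | 1.36 | 0.88 |
| 1033 | 3% | 1.0 | 0.25–0.36 | 2.6 | 0.58 |
| 1033 | 20% | 6.9 | 0.63–0.68 | 1.30–1.33 | 0.92 |
| 1033 | 25% | 8.6 | 0.68–0.70 | – | – |
| 3000 | 3% | 3 | 0.56 | – | – |
| 3000 | 25% | 25 | 0.89–0.95 | 1.00–1.02 | – |
| 5000 | 3% | 5 | 0.69–0.74 | 1.30–1.31 | 0.90 |
| 5000 | 20% | 33 | 0.92–0.94 | 1.00–1.01 | 0.99 |
| 6000 | 3% | 6 | 0.71 | – | – |
| 6000 | 25% | 50 | 0.97 | – | – |
| 20,000 | 3% | 20 | 0.88–0.89 | 0.98–1.01 | 0.99 |

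(The odds ratio 1.5 column used 10 true predictors, except 5 at n = 787 with 25% events.)

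**What a slope of 0.62 means.** At n = 787 and 25% events, the top risk decile was predicted 48% and observed 39%. Check: logit(0.48) − logit(0.25) = −0.080 + 1.099 = 1.019; 0.62 × 1.019 = 0.632; −1.099 + 0.632 = −0.467, which is a risk of 38.5%.

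**AIC instead of p ≤ 0.05.** For one parameter AIC corresponds to p ≤ 0.157. At n = 787 and 25% events, inflation fell from 34% to 22%, but the slope stayed at about 0.63.

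**Uniform shrinkage and points.** If points are S × β_j / Σ|β|, multiplying every β by c cancels. In simulation, 20-point scores from β and from 0.62 × β were identical in every replicate.

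**The case against.** The best defence is sample size. Section 3.7 calls 1180 well below what is available, Bern adds 1550 patients to multicentre CAMUS data, and section 4.3 relies on large samples. This stands for common outcomes in several thousand patients, where the slope is about 0.9 to 1.0. It does not cover the rest of the plan. One-third of the data is held out, separate models are planned for cystectomy, prostatectomy and partial nephrectomy (4.2), one comparison develops on two years of data (4.1), mortality is modelled on its own, and parameters found only in Bern can be fitted on at most 1550 patients.

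Some stronger readings are tempting, and the documents do not support them:

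- That the weights are certainly inflated. The CAMUS sample size and the event rates are not stated, and 787 derives from a calculated minimum, not from the data in hand.
- That every risk read from the score is too extreme. Section 4.1 regresses outcomes on the finished score as an ordered category across three cohorts. Risks re-estimated in cohorts other than the development one do not inherit the inflated scale of β. The problem applies to risks taken directly from the regression models and, through unequal inflation, to the relative points.
- That section 4.3 makes a false claim. It states an aim, not a result.
- That the calculator rests on β alone. Sections 3.5 and 3.6 add expert weights.

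It can also be said that shrinkage is detail for an analysis plan, and that the split-sample checks and the intended external validation would reveal miscalibration. But section 4.1 does not leave the matter open: it fixes unshrunk β as the weights. Revealing a problem is not correcting it, and no action is tied to a poor result.

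**Conclusion.** The concern holds in conditional form. Section 4.1 fixes a method that takes weights from selected, unshrunk coefficients, and nothing stated corrects the slopes. Weights and directly computed risks can be too extreme, mainly for rare outcomes such as mortality, for procedure-specific models and for Bern-only parameters.

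At odds ratio 1.2 with 30 candidates, the calibration slope is about 0.6 to 0.7 with 800 to 1000 development patients and 20 to 25% events, and 0.56 to 0.74 with 3000 to 6000 patients and 3% events. At odds ratio 1.5 it is milder: 0.87 to 0.92 in the first setting and 0.90 at n = 5000 in the second. With several thousand patients and common events little correction is needed. These figures rest on assumed event rates and independent normal predictors. The absence of any slope correction rests on the text alone. The change is worth making before the score is built.

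**What to change.** 1. In section 4.1, estimate the coefficients that become points by penalised (for example ridge) logistic regression on the Delphi-consensus candidate set. This changes relative weights, which a uniform factor cannot do on a fixed 10- or 20-point scale. In simulation, cross-validated ridge gave slopes near 1 at 25% events but under-spread risks at rare events (slopes 1.2 to 1.6), so report the calibration slope.
2. For calculators that use the regression linear predictor, an alternative is to multiply β by a bootstrap shrinkage factor, with screening and selection repeated in each resample, and to re-estimate the intercept. In simulation (48 replicates, 25 resamples) this moved the slope from 0.61 to 0.90 (n = 787, 25% events), from 0.68 to 0.94 (n = 1033, 25%) and from 0.36 to 0.63 (n = 1033, 5%). In large samples the factor will be close to 1 and do no harm.
3. Reword the end of section 4.3 so that the split and the bootstrap ranking are checks on overfitting, and the penalisation or shrinkage step is what reduces it.

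Cost: a little more analysis work and no new data. Apparent discrimination and the spread of predicted risks will look slightly less favourable.
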